### Sample size

We used a sample size calculator for the cluster RCT and a practitioner’s guide to sample size and power calculation by McConnell and Vera-Hernandez [26] to estimate sample size and power for this study. Given the absence of similar studies in Cambodia, our assumptions were based on those used in a similar study in India with some adjustments. We assumed the intra-cluster correlation (ICC) to be 0.02 and the effect size of 13%, slightly below the 15% in India [18]. We observed that the MCH coverage index constructed from indicators of at least four ANC visits, PNC visits in the first 2 days after delivery, and complete immunization of children aged 12–24 months in 2021 in our selected provinces is at 70%, higher than the 36% of the MCH composite index in India [27]. Our cluster size was approximately 200, assuming there are two HCs per operational district, 10 villages per HC, and 10 mothers or pregnant women per village. The confidence level was set at 95%, while each arm consisted of five clusters. After obtaining a sample of 1858 mothers (929 per arm) and a power of 85%, we accounted for a 5% non-response rate and arrived at a sample size of 1951 mothers for both arms.

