APNC will consist of four sub-components: (1) the proportion of mothers visited by VHSGs at least three times in the last pregnancy, (2) the proportion of mothers with at least four ANC visits in the last pregnancy and one tetanus vaccine injection, (3) the proportion of mothers delivered at a health facility (public or private), and (4) the proportion of mothers with at least three PNC visits in the last pregnancy. IMMU will consist of two sub-components: (1) the proportion of young infants aged 12–24 months fully vaccinated based on the national guideline with one dose of Bacillus Calmette–Guérin (BCG) vaccine for tuberculosis; three doses of polio vaccine given as oral polio vaccine (OPV), inactivated polio vaccine (IPV), or combination of OPV and IPV; three doses of diphtheria, pertussis, and tetanus (DPT) vaccine; and one dose of measles vaccine given as measles-rubella (MR) and (2) the proportion of young infants exclusively breastfed in the first 6 months. TREAT will consist of three sub-components: (1) the proportion of neonates with complications in the first month of the last delivery who seek care from VHSGs, (2) the proportion of infants aged two to 24 months with diarrhea in the last 2 weeks and receiving oral rehydration therapy (ORT) from VHSGs, and (3) the proportion of infants aged 2 to 24 months with acute respiratory infections in the last 2 weeks and seeking care from VHSGs.

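### The stated 85% power belongs to a three-indicator proxy at 70% versus 83%, not to the nine-item primary MCH index, whose power could be lower or higher

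*Protocol article*

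**What the plan says.** The Sample size section sets the starting level on an "MCH coverage index constructed from indicators of at least four ANC visits, PNC visits in the first 2 days after delivery" and complete immunization at 12–24 months. It reports that this index "in our selected provinces is at 70%, higher than the 36% of the MCH composite index in India". The other inputs are: "We assumed the intra-cluster correlation (ICC) to be 0.02 and the effect size of 13%, slightly below the 15% in India"; "Our cluster size was approximately 200, assuming there are two HCs per operational district"; and "The confidence level was set at 95%, while each arm consisted of five clusters". The result is 929 mothers per arm (1858 in all) at 85% power, raised to 1951 for 5% non-response.

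The Primary outcomes section builds the MCH-CI from three equally weighted blocks.

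- **APNC:** "APNC will consist of four sub-components: (1) the proportion of mothers visited by VHSGs at least three times in the last pregnancy"; mothers "with at least four ANC visits in the last pregnancy and one tetanus vaccine injection"; delivery in a health facility; and at least three PNC visits.
- **IMMU:** full vaccination at 12–24 months, and exclusive breastfeeding for six months.
- **TREAT:** three items on ill neonates or infants, each counting care or treatment obtained from VHSGs.

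The same section says that effectiveness will be judged on the MCH coverage index, the name the Sample size section gives to its three-indicator measure.

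**The concern.** The sample size and the primary outcome use one name for two constructs. The Sample size section also sets its 70% beside the Indian composite index as if the two were the same measure. A reader will attach the 85% to the MCH-CI, although the calculation contains no information on the level or spread of that index. If the result is null, the 85% may be read as evidence that a 13-point gain on the MCH-CI would probably have been detected. The calculation does not support that reading.

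**Working it through.** **1. Reproduce the plan's figure.** Inputs from the Sample size section: control 0.70, gain 0.13 (so 0.83), two-sided alpha 0.05, power 85%, ICC 0.02, cluster size 200.

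- Design effect = 1 + (200 − 1) × 0.02 = 4.98.
- n before clustering = (1.960 + 1.036)² × (0.70×0.30 + 0.83×0.17) / 0.13² = 8.978 × 0.3511 / 0.0169 = 186.5.
- n per arm = 186.5 × 4.98 = 929; total 1858; 1858 × 1.05 = 1951.

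All three stated figures are reproduced. Other readings are not: a relative gain of 13% (70% to 79.1%) needs 2026 per arm, and 36% to 49% needs 1271. The 70% therefore drives the stated sample size.

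**2. Compare the two indices.** Weights follow from the formula in Primary outcomes: 1/3 × 1/4 = 1/12 for each APNC item, 1/3 × 1/2 = 1/6 for each IMMU item, and 1/3 × 1/3 = 1/9 for each TREAT item.

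| MCH-CI item | Weight | In the 70% proxy? |
|---|---|---|
| At least 3 VHSG visits in pregnancy | 1/12 | No |
| At least 4 ANC visits plus tetanus injection | 1/12 | ANC only, no tetanus condition |
| Facility delivery | 1/12 | No |
| At least 3 PNC visits | 1/12 | Different: PNC in the first 2 days |
| Full vaccination, 12–24 months | 1/6 | Yes |
| Exclusive breastfeeding | 1/6 | No |
| Three TREAT items, care from VHSGs | 3 × 1/9 | No |

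Absent weight = 1/12 + 1/12 + 1/6 + 3/9 = 2/3. The part on VHSG contact or care = 1/12 + 3/9 = 5/12.

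**3. Power at 929 per arm for other baselines, on the plan's own formula.** The effective n is 929/4.98 = 186.5 per arm. Power = Φ(0.13 / √[(p₁q₁ + p₂q₂)/186.5] − 1.96), with p₂ = p₁ + 0.13. The 13-point gain is held fixed by assumption. The documents give no baseline for the MCH-CI, so every row below 70% is an assumption.

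| Baseline | Power at 929 per arm | n per arm for 85% |
|---|---|---|
| 70% | 85.0% | 929 |
| 60% | 76.6% | 1156 |
| 59.1% | 76.1% | 1172 |
| 56.4% | 74.6% | 1212 |
| 49.4% | 72.3% | 1282 |
| 40% | 71.9% | 1294 |
| 36% | 72.6% | 1271 |
| 20% | 82.0% | 1008 |
| 10% | 93.0% | 707 |

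The 59.1%, 56.4% and 49.4% are national figures that Primary outcomes quotes for other coverage measures; 36% is the Indian index. The variance term is largest where p₁ + p₂ = 1, at p₁ = 0.435, so power on this formula does not fall below about 72% for a 13-point gain.

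**4. If the index is scored as a mean on 0–100.** Power = Φ(13 / [SD × √(2/186.5)] − 1.96), again for 13 points, with assumed SDs.

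| SD (points) | Power |
|---|---|
| 30 | 98.7% |
| 40 | 88.1% |
| 42 | 84.8% |
| 50 | 70.9% |

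Solving for 85% gives SD = 13 / (2.996 × √(2/186.5)) = 41.9 points. The result also depends on the gain: at 8 points and SD 30, power is 73.1%.

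Steps 3 and 4 keep the plan's ICC, cluster size and normal approximation, so that only the index changes. They assume that all 929 mothers per arm contribute. The TREAT items apply only to ill children and the vaccination item only to ages 12–24 months, so the denominators of those items are smaller.

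**The case against.** The strongest reply is that the proxy is disclosed. The Sample size section names the three indicators, the year and the provinces, and says that assumptions were borrowed because no similar Cambodian study existed. Using available survey indicators at the planning stage is reasonable. This stands as a defence of the choice. It does not make the 85% a statement about the MCH-CI, and no sentence says that it is not one.

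A second reply is that no direction of error can be shown, and this stands in full. A reader might infer that the MCH-CI must start far below 70%, because VHSG items are likely to be rare, and hence that the trial is underpowered at about 72–77%. The documents give no level for any VHSG item and no SD for the index. The 36–60% range surrounds the maximum of the variance term, so it is close to the worst case of that formula. An index averaged over items need not have binomial variance. The VHSG items are also what the intervention targets, so the gain might change along with the baseline.

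A reader might also infer that the assumed effect comes from a different endpoint than the baseline. The article attaches different references to the 15% effect and the 36% index ([18] and [27]). Which measure the 15% describes cannot be settled from the text. Nor is the PNC item simply stricter: three visits could all fall after day 2, so the two criteria differ without one containing the other.

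The point does not rest on something left to a statistical analysis plan. The article states both the sample size basis and the primary index, and they do not match.

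**Conclusion.** The mismatch is certain. The calculation behind 929 per arm and 85% power is for a three-indicator proxy at 70% versus 83%, and it reproduces the stated figure. The proxy shares one item, of weight 1/6, largely unchanged with the MCH-CI. It has related but differently defined items for a further 1/6 (ANC and PNC), and lacks the remaining 2/3. The 85% is therefore not the power for the primary index.

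The size and sign of the discrepancy are not fixed by the documents. For a 13-point gain, the assumptions shown give about 72% to 93% on the binomial formula over baselines of 10–70%, and about 71% to 99% on a mean score with SDs of 50 down to 30 points. The documents do not support replacing 85% with any single other number, or saying that power necessarily becomes less favourable.

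**What to change.** In the Sample size section, state that the 70% and the 85% refer to a three-indicator proxy and not to the MCH-CI, and give the proxy a name of its own. Present the Indian 36% as a different measure or omit the comparison.

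Then use the planned baseline household survey to estimate the level and variance of the MCH-CI as defined in Primary outcomes, including its between-OD variance. State whether the index is handled as a proportion or as a mean score, and restate the power or the detectable difference at the fixed sample. Only ten ODs contribute to the between-OD variance, so that estimate will be imprecise and the restated figure should come with a range. Until the baseline data are in, show power over the full set of assumed baselines or SDs, including values where it exceeds 85%.

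The cost is one recalculation and a few sentences. No change in enrolment is needed.

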#### Primary outcomes

VHSGs will facilitate the primary outcomes of interest throughout the continuum of care, including (1) the proportion of neonates/mothers visited at home by VHSGs at least twice within the first week of delivery, (2) the proportion of mothers receiving information from VHSGs regarding danger signs of newborn illnesses within the first week of delivery, and (3) the MNCH composite coverage index, consisting of four dimensions, namely maternal care, neonatal care, infant care, young childcare, and care-seeking when having complications.

The MCH composite index was initially introduced by Boerma et al. [31, 32]. It captures a complete continuum of care of mothers and children by including four dimensions: family planning, maternal and newborn care, immunization, and treatment of children. Following Modi et al. [27], we will exclude family planning to focus more on the role of the VHSGs in evaluating the effectiveness of mobile health technology. The three components will be equally weighted. The index will be calculated using the following formula: MCH-CI = 1/3 (¼ APNC + ½ IMMU + 1/3 TREAT), where APNC denotes antenatal and postnatal care, IMMU denotes immunization among children, and TREAT denotes the treatment of children. The index will vary between 0 and 100, with a higher index score indicating a higher MCH coverage. We will use the MCH coverage index to evaluate the effectiveness of the intervention. We have conjectured that the coverage rate should be well above 60% to be meaningful since earlier estimates of the compelling national coverage of maternal health services (ANC and facility delivery) and sick childcare (diarrhea, pneumonia, and fever) in 2014 were 56.4% and 59.1%, respectively [33]. Another recent study using a slightly deviated measure of the mother and infant care continuum shows that the national coverage was 49.4% [34].

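### The stated 85% power ignores that only five districts per arm are randomized; on the same inputs an unpaired cluster-level comparison has about 75–77%

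*Protocol article*

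**What the plan says.** The Sample size section gives these inputs: "We assumed the intra-cluster correlation (ICC) to be 0.02 and the effect size of 13"%; a coverage level that "in our selected provinces is at 70"%; and "Our cluster size was approximately 200". It adds: "The confidence level was set at 95%, while each arm consisted of five clusters". The result is given as: "After obtaining a sample of 1858 mothers (929 per arm) and a power of 85"%. The section mentions no adjustment for the small number of clusters.

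The Randomization section makes the OD the randomized unit, allocated within five matched pairs of provinces. The Analysis plan says that the matching has to be taken into account. It also recognises that 10 ODs is a small number and plans finite-sample-corrected GEE as a further analysis.

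The 70% is built from three indicators: four or more antenatal visits, a postnatal visit within two days, and complete child immunization. The primary index, defined under Primary outcomes, has nine sub-components. One of them is "the proportion of mothers visited by VHSGs at least three times in the last pregnancy"; others are at least three postnatal visits, exclusive breastfeeding, and care for sick children sought or received from VHSGs.

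**The concern.** Multiplying an individually randomized sample size by a design effect corrects the variance for clustering. It does not correct the reference distribution. With 10 randomized units, the between-district variance is estimated on 8 degrees of freedom, or on 4 if the five pairs are analysed as pairs. The critical value is then 2.306 or 2.776, not 1.960, and power falls accordingly.

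The Analysis plan accepts that small-sample correction is needed for valid standard errors, but that correction is not carried back into the power statement. The 85% therefore describes a test that the plan itself regards as unreliable with so few clusters. At stake is how the result is read: a null finding would be given more weight as evidence against a 13-point effect than the design supports.

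Separately, the base level was computed for one index, while the trial will be analysed on another.

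**Working it through.** **Inputs (Sample size section):** control level 0.70; effect 13%; ICC 0.02; cluster size about 200; five clusters per arm; 95% confidence; 85% power. The text does not say that the test is two-sided or that the 13% is absolute. Both are inferred, because together they reproduce the stated sample size exactly.

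**Step 1. Reproduce the plan's figure.**
- Variance sum: 0.70×0.30 + 0.83×0.17 = 0.2100 + 0.1411 = 0.3511.
- Individually randomized n per arm: (1.960 + 1.036)² × 0.3511 / 0.13² = 186.53.
- Design effect: 1 + (200 − 1)×0.02 = 4.98.
- 186.53 × 4.98 = 928.9, rounded up to 929 per arm and 1858 in total. Exact match.

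Other forms do not give 929. With the same design effect, pooled variance gives 946, a continuity correction 1021, 57% against 70% gives 1204, and a relative 13% (70% against 79.1%) gives 2027. A formula fixing five clusters per arm gives 720. The stated 85% therefore rests on normal quantiles.

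**Step 2. Noncentrality on the same inputs.** There are two defensible versions:
- Plan's design effect applied to 929: effective n = 929/4.98 = 186.5; standard error = √(0.3511/186.5) = 0.0434; noncentrality = 0.13/0.0434 = 3.00.
- Cluster size implied by 929 (929/5 = 185.8): design effect = 1 + 184.8×0.02 = 4.696; effective n = 197.8; standard error 0.0421; noncentrality 3.09.

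**Step 3. Power from the noncentral t distribution, two-sided 0.05.**

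| Reference | Noncentrality 3.00 | Noncentrality 3.09 |
|---|---|---|
| Normal | 85.0% | 87.0% |
| t, 8 df (10 − 2, unpaired) | 74.7% | 77.1% |
| t, 4 df (5 − 1, paired, no gain from matching) | 61.8% | 64.2% |

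A full 1000 per arm gives only 77.7% (8 df) and 64.9% (4 df). A beta-binomial simulation of cluster-mean t-tests (200,000 trials per setting, 186 per cluster) gives 77.1% and 64.5%.

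**Step 4. Detectable difference at 85% power.** The noncentrality required is 3.427 (8 df) or 4.041 (4 df). Solve d / √([0.21 + (0.70 + d)(0.30 − d)] / effective n) for d:
- 8 df: d = 0.146 (effective n 186.5) or 0.143 (197.8).
- 4 df: d = 0.168 or 0.164.

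**Step 5. How much matching would have to contribute.** On 4 df, matching must cut the variance of the difference by 1 − (3.086/4.041)² = 42% to 1 − (2.996/4.041)² = 45% to reach 85%. A cut of about 27% is needed just to equal the 8-df power. The documents give no matching correlation.

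**The case against.** **Small clusters are already handled at analysis.** The Analysis plan names the problem and proposes corrected GEE and covariate adjustment. This is true and to its credit, but it concerns the standard errors at analysis. The power figure is unaffected and remains uncorrected.

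**A paired 4-df test is not specified.** This stands. The plan says that matching serves balance and does not create a matched dataset, and then that the analysis must take it into account. That does not amount to a paired t-test. A reader might infer that true power is 62–64%; this holds only if the analysis is paired and matching removes no between-district variance.

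**Baseline data may restore power.** The main analysis is a difference-in-difference, which could raise or lower power depending on how strongly district effects at baseline and endline correlate. The Sample size section credits no baseline data and gives no such correlation, so no difference-in-difference power can be derived from the documents. Village-level standard errors, also planned, lie below the randomized unit and cannot rescue the figure without risking type I error.

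**Three further readings go beyond the documents.**
- The effect is described as "the effect size of 13%, slightly below the 15% in India". A reader might object that it is larger than the Indian effect on the odds scale. That needs a choice of scale and details of sources that are not shown; in points, 13 is below 15.
- A reader might replace 70% by the lower national figures, such as the study that "shows that the national coverage was 49.4"%. Those are other measures, so they do not supply the base level of the primary index.
- The non-response inflation multiplies by 1.05 (1858 × 1.05 = 1951) where dividing by 0.95 gives 1956. Five mothers is immaterial, and the nominal 200 per OD across 10 ODs exceeds both.

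**Conclusion.** The point holds in this form. The 85% is a normal-quantile result; with five ODs per arm and otherwise unchanged inputs, power is 74.7–77.1% on 8 df, so it is overstated by roughly 8 to 10 percentage points. The detectable difference is 14.3–14.6 points. The 4-df figures (61.8–64.2%; 16.4–16.8 points) are conditional on a paired analysis with no gain from matching and should be labelled so.

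All these figures rest on a two-sided test, an absolute 13-point effect, ICC 0.02, and the plan's own binary variance. That variance may not fit a weighted average of nine coverage indicators, and the 70% belongs to a different index. In which direction the correct base level and variance would move power cannot be settled from the documents.

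**What to change.** Keep the sample. In the Sample size section:

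1. Replace the 85% by power computed with cluster-level degrees of freedom for the test that will be used, and say which test that is. On the present inputs this is about 75–77% if unpaired. If paired, give the figure together with its assumption about matching.
2. Report the matching detectable difference at 85% power (14.3–14.6 points unpaired), and state the two-sided test and the absolute scale of the effect.
3. If matching or baseline adjustment is credited, state the assumed matching correlation or baseline–endline correlation of OD effects, with a range.
4. Recompute the base level and the variance for the actual primary index from the baseline survey, and update the power statement.

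The cost is one recalculation and some rewording. No participants are added and the design does not change, but on the present inputs the stated power becomes less favourable.

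### The 5% non-response allowance multiplies by 1.05 instead of dividing by 0.95, so approaching 1951 mothers leaves about 5 fewer than the required 1858

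*Protocol article*

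**What the plan says.** Everything needed is in the Sample size section of the protocol article. The assumptions are stated there: "We assumed the intra-cluster correlation (ICC) to be 0.02 and the effect size of 13"%, with an MCH coverage index that "in our selected provinces is at 70"%, a 95% confidence level and five clusters per arm. The cluster size is put at roughly 200, on the assumption of "two HCs per operational district, 10 villages per HC, and 10 mothers or pregnant women per village".

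The result comes in two steps. The first is the number needed for analysis: "After obtaining a sample of 1858 mothers (929 per arm) and a power of 85"%. The second is the allowance: "we accounted for a 5% non-response rate and arrived at a sample size of 1951 mothers for both arms". The article does not say how the 5% was applied.

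**The concern.** An allowance for non-response has one job: after the expected losses, the number left should be at least the number the power calculation asked for. With a non-response rate d, expressed as a share of those approached, the number to approach is n / (1 − d). Multiplying by (1 + d) always gives a smaller number, because (1 + d)(1 − d) = 1 − d², which is below 1. The stated total matches the multiplicative form.

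Very little is at stake at d = 5%, since d² is only 0.0025. The reason to raise it is that the total sample size is a headline figure that will be carried into later reports, and as printed it falls short of the requirement given in the same sentence.

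**Working it through.** **Inputs (all from the Sample size section).** Required sample 1858 (929 per arm); power 85%; non-response 5%; final total 1951; baseline 70%; effect 13%; ICC 0.02; cluster size about 200; five clusters per arm; 95% confidence. Two readings are assumed: a two-sided 0.05 test, and 13 percentage points (70% against 83%). The second is the reading that reproduces the plan's figure. A relative 13% increase, to 79.1%, would need about 2027 per arm.

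**Step 1: reproduce the required sample.**

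- Unpooled two-proportion formula: n = (1.960 + 1.036)² × (0.70 × 0.30 + 0.83 × 0.17) / 0.13² ≈ 8.978 × 0.3511 / 0.0169 ≈ 186.5 per arm.
- Design effect: 1 + (200 − 1) × 0.02 = 4.98.
- 186.5 × 4.98 ≈ 929 per arm, or 1858 in total. This agrees with the article.

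**Step 2: reproduce the inflated total.**

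| Method | Calculation | Total |
|---|---|---|
| Multiply by 1 + d | 1858 × 1.05 = 1950.9 | 1951 (as stated) |
| Divide by 1 − d | 1858 / 0.95 = 1955.8 | 1956 |

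Per arm, division gives 929 / 0.95 = 977.9, rounded up to 978, and 2 × 978 = 1956. The stated 1951 is an odd number and does not split equally between the arms.

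**Step 3: expected respondents.**

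- 1951 × 0.95 = 1853.4, which is 4.6 below 1858.
- 1956 × 0.95 = 1858.2, which meets 1858.
- The gap in the number to approach is 1956 − 1951 = 5, and 5 / 1951 = 0.26%.

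**Step 4: effect on power.** This uses 70% against 83%, ICC 0.02, the normal approximation with pooled variance under the null, and the design effect at the realised cluster size.

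- 929 per arm: cluster size 185.8, design effect 4.696, effective n = 929 / 4.696 = 197.83, power 86.49%.
- 926.7 per arm (half of 1853.4): cluster size 185.3, design effect 4.687, effective n = 197.73, power 86.47%.
- Change: 0.02 percentage points.

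Both values exceed 85% because about 186 women per cluster gives a smaller design effect than the 200 used in Step 1. A t reference with 8 degrees of freedom lowers the level, to 77.11% and 77.09%, but the change is again 0.02 points. Which reference is right is a separate question and does not affect this point.

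**The case against.** The strongest objection is that the difference does not matter. Rounding 186.5 up to 187 before applying the design effect gives 931 rather than 929 per arm, which moves the total by about as much as this error does. The pooled formula gives 946 per arm, which adds 34 in total. The required total changes by about 2 × 186.5 × 199 ≈ 74,200 per unit of ICC, so 5 women correspond to an ICC change of 5 / 74,200 ≈ 0.00007 on an assumed 0.02. All of this stands, and it fixes the severity. It does not make 1951 the right answer to the sentence it sits in.

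A second objection is that 1951 could mean completed interviews, in which case it exceeds 1858. But a figure reached by adding an allowance for non-response is naturally the number to approach, and the shortfall is stated on that reading. One could also define the 5% as a share of respondents. The implied loss among those approached would then be (1951 − 1858) / 1951 = 93 / 1951 = 4.8%, which is not what a 5% non-response rate ordinarily means.

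A reader might also infer something stronger from the cluster-size assumption. Ten clusters of 200 make 2000, so the plan might seem to hold a quota of 2000 that conflicts with 1951, leaving field teams with two targets; and 1951 / 200 villages = 9.76 women per village might seem impossible to sample. The document does not support this:

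- It nowhere states 2000 women as a quota or a field target. The 200 is an approximate planning input to the design effect.
- 1951 / 10 = 195 per cluster, which fits an approximate 200.
- No fixed take per village is specified. The household survey section names only a village household list as the sampling frame, and taking 10 women in most villages and 9 in some averages 9.76.
- If about 2000 women were in fact approached, 2000 × 0.95 = 1900 would respond and the shortfall would disappear.

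**Conclusion.** The point holds as a small arithmetic error. The stated 1951 equals the required 1858 multiplied by 1.05; division by 0.95 gives 1956. This rests on two assumptions: that 1951 is the number of mothers to approach, and that 5% is the share of them who do not respond. The multiplication itself is inferred from the match, because the article does not print the formula.

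The practical effect is nil, at roughly half a woman per cluster. It would be wrong to conclude from this that the trial is underpowered or that the fieldwork plan contradicts itself. The severity is the lowest available.

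**What to change.** Make one of two changes in the Sample size section:

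- Restate the number to approach as 1956 mothers (978 per arm), and give the formula, 1858 / 0.95.
- Or keep 1951 and add that about 1853 respondents are expected at 5% non-response, accepting that this is slightly under 1858.

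The first is cleaner, since it meets the stated requirement and divides equally between the arms. It costs one corrected figure and at most five more women to approach across ten operational districts. Nothing in the randomization, the choice of clusters or the analysis changes.
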